**Figure 1 F1:**
[figure not shown]
Study algorithm. eGFR, estimated glomerular filtration rate; Hx, History of …; LDL-C, low-density lipoprotein-cholesterol; NSTEMI, Non-ST-segment myocardial infarction; STEMI, ST-segment myocardial infarction.

Group A will consist of the subgroup of patients who do not reach the LDL-C guideline target [LDL-C < 1.4 mmol/L (55 mg/dL)] after 6 weeks and will receive additive bempedoic acid (180 mg/day) for another 8 weeks (Triple therapy). Group B will consist of the subgroup of patients who achieve the LDL-C guideline target after 6 weeks of treatment with atorvastatin plus ezetimibe and who will continue on dual therapy for another 8 weeks (Dual therapy).

The 6-week escalation interval reflects local healthcare system, including certain reimbursement constraints, while aligning with evidence-based preferences to minimize delays in treatment intensification.

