### Study population and inclusion

The study population will comprise up to 135 patients aged ≥18 and ≤85 years following acute percutaneous coronary intervention for STEMI or non-STEMI (NSTEMI), all on high-intensity oral lipid-lowering therapy. Importantly, baseline parameters will be used to demonstrate that patients enrolled in the HACOL-ACS trial are representative of a real-world cohort described previously at our institution, which showed mean LDL-C levels of 3.9 ± 0.7 mmol/L (149 ± 27 mg/dL) (7).

Inclusion criteria for the trial are as follows: patients of all sexes aged between 18 and 85 years, who have provided written informed consent, had NSTEMI or STEMI with successful coronary intervention within 7 days prior to screening, have a therapy-naïve LDL-C > 2.6 mmol/L (100 mg/dL), and are able to cooperate with the protocol regimen and follow-up.

Exclusion criteria are as follows: history of gout, scheduled surgery within the next 4 months, inability to attend study site revisits, participation in another clinical trial within 30 days prior to study start or during the trial, known hypersensitivity to any of the components of the medications used, pregnancy or breastfeeding, severe renal disorders (defined as estimated glomerular filtration rate <30 mL/min/1.73 m^2^) or requiring dialysis for end-stage renal disease, history of tendon disorders or tendon rupture, or requirement for placement in a mental institution by court or official order.

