#### Study intervention/treatment

After the index hospitalization and enrolment into the trial, standard medication including atorvastatin (40 mg/day) and ezetimibe (10 mg/day) will be recommended. After 6 weeks (Stage I), a study visit will be conducted at the institution and another lipid test will be performed. Next (Stage II), study medication (bempedoic acid, 180 mg/day, provided by Daiichi Sankyo, Munich, Germany) will be given at V2 to patients with LDL-C 1.4-2.8 mmol/L (55-110 mg/dL) (Group A), and patients with LDL-C < 1.4 mmol/L (55 mg/dL) will be continued on the background medication with the previous dosing (Group B). Patients with LDL-C > 2.8 mmol/L (110 mg/dL) at week 6 will be directly referred for PCSK9 inhibition outside the trial. Patients with LDL-C ≤ 2.8 mmol/L (110 mg/dL) mg/dL will have a revisit (V3) after another 8 weeks, including another lipid test.

The dose of bempedoic acid— 180 mg/day—will not be modified. The background medication is atorvastatin (40 mg/day) plus ezetimibe (10 mg/day), which is the standard discharge medication. If—despite explanation about the study protocol—patients are escalated by their treating physicians to higher doses of atorvastatin (>40 mg/day) or switched to rosuvastatin (minimum 20 mg/day), this will be considered stable baseline medication with regard to the study protocol. Switching between medications and de-escalation of statin treatment are strongly discouraged. A sensitivity analysis excluding patients with escalated doses of atorvastatin or switching to equal doses of rosuvastatin is planned.

Remaining study medication will be counted upon return at V3. Aside from adherence to lipid-lowering therapy, no other restrictions apply to routine care.

This strategy reflects current guideline recommendations to either initiate or escalate to a dual lipid-lowering therapy with a high-dose potent statin in combination with ezetimibe prior to adding a third compound (17). It also supports the generalizability of HACOL-ACS results to broader patient populations.

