#### Study endpoints

The primary endpoint is defined as the proportion of patients (%) in Group A who successfully achieve the European Society of Cardiology (ESC) LDL-C guideline target after Stage II. Secondary endpoints comprise the following: proportion of patients (%) who successfully achieve ESC LDL-C guideline targets [LDL-C < 1.4 mmol/L (55 mg/dL)] after treatment with dual therapy including atorvastatin (at least 40 mg/day or equivalent) plus ezetimibe (10 mg/day) at 6 and at 14 weeks; the proportion of patients (%) who successfully achieve the ESC LDL-C guideline targets after 14 weeks of treatment; the proportion of patients (%) who achieve American heart Association (AHA)/American College of Cardiology (ACC) guideline-recommended treatment targets of LDL-C < 1.8 mmol/L (70 mg/dL) after 14 weeks of treatment in the triple therapy group; mean change from baseline to week 6 and week 14 in LDL-C, total cholesterol, HDL-C, triglycerides, uric acid, creatine kinase, systolic and diastolic blood pressure, and heart rate; the proportion of non-compliant patients (%) taking less than 90% of the allocated study medication; and mean change from baseline to week 6 and to week 14 in quality of life.

Safety will be assessed by monitoring and recording all adverse events, serious adverse events, and certain laboratory parameters (further described under pharmacovigilance).

The primary endpoint was chosen to focus on the efficacy of the investigational compound in order to prevent that a higher than anticipated achievement rate of the LDL-C target on the baseline medication might result in an escalation subgroup being too small to conduct proper statistical analyses.

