## Statistical analysis

All analyses will be descriptive and performed in the ITT population. Demographic and baseline measurements will be summarized using descriptive methods. In the primary analysis, the proportion of responders and an exact descriptive 95% Clopper–Pearson confidence interval (CI) will be calculated. Patients with missing values for the primary endpoint will be counted as treatment failures in the ITT analysis, that is, as patients who did not achieve LDL-C guideline targets of <1.4 mmol/L (55 mg/dL) after treatment for 14 weeks.

Explanatory analyses for secondary endpoints will be carried out separately for Groups A and B. Responder rates will be examined using the exact 95% Clopper–Pearson CIs, and continuous data will be compared exploratorily using two-sided paired *t*-tests, with a two-sided level significance of 5%. In addition, mean changes in continuous laboratory parameters will be compared between Groups A and B using an analysis of covariance model, including baseline values at the start of the study and group assignment.

For the primary endpoint, a subgroup analysis will be carried out. Patients in the triple therapy group who fail to achieve the LDL-C guideline target of LDL-C < 1.4 mmol/L (55 mg/dL) after Stage I will be divided into four subgroups depending on their LDL-C level:
Group: LDL-C of 55 – ≤ 68.75 mg/dL (1.4–≤1.8 mmol/L).Group: LDL-C of 68.75 – ≤ 82.5 mg/dL (1.8–≤2.1 mmol/L).Group: LDL-C of 82.5 – ≤ 96.25 mg/dL (2.1–≤2.5 mmol/L).Group: LDL-C of 96.25 – ≤ 110 mg/dL (2.5–≤2.8 mmol/L).In every subgroup, the proportion of responders will be examined and exact 95% Clopper–Pearson CIs will be calculated. To evaluate the robustness of the results, efficacy analyses will be repeated in the PP population (sensitivity analyses).

Descriptive analyses will be performed to assess adverse events and serious adverse events. As this is an exploratory study, no adjustment for multiplicity will be performed. Confidence intervals and respective *p*-value will only be assessed descriptively.

Access to the final trial dataset will be centralized at the Center for Clinical Trials.

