## Limitations

The study has a single-center, open-label, non-randomized design, which introduces potential bias. For example, the single-arm design inherits the risk that changes in food intake, general lifestyle, and background medication over time may influence LDL-C and, thereby, the estimate of LDL-C-lowering effects of bempedoic acid. Hence, our study is exploratory regarding the escalation strategy and non-comparative.

HACOL-ACS is a short-term feasibility trial testing the applicability of sequential add-on bempedoic acid when guideline-recommended LDL-C targets are not achieved with tolerated high-intensity statin treatment combined with ezetimibe. The purpose of the trial is to describe the extent of additive LDL-C lowering provided by the sequential escalation. Given the small sample size and short duration, the trial does not assess long-term outcomes and, therefore, relies on surrogate endpoints, limiting clinical inference.

The single-center design and the fact that the study will be conducted within a specific healthcare system with defined prescribing constraints will impact but not prevent external validity and applicability to other settings. However, these prescribing constraints would have similar applicability even in a multicenter trial in a single country. The constraints on lipid-lowering therapy, however, allowed for prescription of atorvastatin, rosuvastatin, and ezetimibe, which will allow to use the most potent statins.

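### The exploratory A-versus-B ANCOVA of LDL-C change adjusts only for study-start values, although the groups are formed by week-6 LDL-C, so its group term mixes the drug effect with selection on response

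*Protocol article*

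**What the plan says.** All places are in the protocol article.

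- **Statistical analysis:** besides the within-group analyses, average laboratory changes are to be "compared between Groups A and B using an analysis of covariance model, including baseline values at the start of the study and group assignment". Week-6 LDL-C is not among the covariates.
- **Study endpoints:** the changes are defined from study start: "mean change from baseline to week 6 and week 14 in LDL-C, total cholesterol, HDL-C, triglycerides, uric acid, creatine kinase".
- **Study design (text under Figure 1):** "Group A will consist of the subgroup of patients who do not reach the LDL-C guideline target" at week 6, and these patients add bempedoic acid. By contrast, "Group B will consist of the subgroup of patients who achieve the LDL-C guideline target after 6 weeks of treatment with atorvastatin plus ezetimibe", and these patients stay on dual therapy.
- **Study intervention/treatment:** Group A is also bounded above: "Patients with LDL-C > 2.8 mmol/L (110 mg/dL) at week 6 will be directly referred for PCSK9 inhibition outside the trial".
- **Limitations:** the section concedes bias from the open-label, non-randomized design and concludes: "Hence, our study is exploratory regarding the escalation strategy and non-comparative". It names diet, lifestyle and background medication as sources of bias. It does not mention selection on week-6 response and does not qualify the ANCOVA.

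**The concern.** ANCOVA with a baseline covariate is a sound way to compare groups when membership is unrelated to the outcome given that covariate. Here membership is decided by the outcome variable, measured six weeks after the covariate. Two patients who both start at 150 mg/dL go to different groups because one responded better to the statin and ezetimibe, or because of measurement noise at V2. The first of these differences persists to week 14, and the model credits it to group.

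The consequences for LDL-C are:

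- At week 6 no bempedoic acid has been dispensed, yet A must exceed B by construction.
- At week 14 the group term is the drug effect (negative) plus the persisting selection difference (positive).

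At stake is a prespecified estimate that can make an effective add-on look useless or harmful. It would appear in the same report that sets out to show the additive effect of bempedoic acid.

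**Working it through.** **The plan's own figure.** The article gives no size or precision for the ANCOVA. Its one sample-size figure concerns the primary endpoint, and it reproduces. The exact Clopper–Pearson limits at 30/60 are 0.3681 and 0.6319, a width of 0.2639, or 26.4%. It is used below only for the group size of 60.

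**Inputs from the article**
- Study-start LDL-C 149 ± 27 mg/dL in the institution's earlier cohort, with inclusion above 100 mg/dL (Study population and inclusion).
- About half of patients miss 55 mg/dL at week 6 (Sample size).
- Those above 110 mg/dL leave at week 6 (Study intervention/treatment).
- Bempedoic acid lowers LDL-C by a further 17% (Background).

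**Assumptions not in the article, shown as ranges**
- Between-patient SD of the percentage reduction on dual therapy: 6, 10 or 15 points.
- Within-patient visit-to-visit CV: 8, 15 or 25%.

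**Model.** Baseline B is N(149, 27) restricted to B > 100. The underlying dual-therapy level is T = B(1 − R). The mean of R is 1 − 55/150 ≈ 63%, where 150 is the median of the restricted baseline, so about half are at or above 55. The observed values at weeks 6 and 14 are T times independent log-normal visit noise. Group A has 55 ≤ week 6 ≤ 110, and its week-14 value is multiplied by (1 − effect). The fitted model is the stated one: (week 14 − B) on B and group, with 400,000 simulated patients per scenario.

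**Decomposition.** At a given baseline,

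A − B at week 14 = drug effect in A + [mean dual-therapy LDL-C given week 6 ≥ 55 − mean dual-therapy LDL-C given week 6 < 55].

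The bracket is positive. A run with no drug effect estimates it.

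| SD (points) / CV (%) | Week 6, A−B | Week 14, no effect | Week 14, 17% effect | True effect in A |
|---|---|---|---|---|
| 6 / 8 | +17.0 | +13.7 | +3.2 | −11.2 |
| 6 / 15 | +20.5 | +11.3 | +0.9 | −11.0 |
| 6 / 25 | +26.6 | +8.3 | −2.1 | −10.9 |
| 10 / 8 | +25.7 | +23.7 | +12.3 | −11.8 |
| 10 / 15 | +27.9 | +21.6 | +10.3 | −11.7 |
| 10 / 25 | +31.6 | +17.9 | +6.8 | −11.5 |
| 15 / 8 | +34.4 | +33.2 | +20.9 | −12.5 |
| 15 / 15 | +35.4 | +31.4 | +19.4 | −12.4 |
| 15 / 25 | +37.3 | +28.3 | +16.4 | −12.3 |

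All values are in mg/dL. Repeat runs put the upper ends slightly higher, at about +38 (week 6), +34 (no effect) and +22 (17% effect).

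**Reading the table**
- Middle case (10 / 15): selection +21.6 plus drug −11.7 gives +9.9, close to the fitted +10.3. The SE with 60 per group is about 2.5.
- The one scenario with the right sign shows −2.1 of −10.9, about a fifth of the true effect.
- The LDL-C reduction needed for the model to show no difference is 14% to 46% (middle case 32%).

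**Alternatives under the same set-up**
- V2-to-V3 change with V2 LDL-C as covariate: −1.4 to +1.1 with no effect, and −8.4 to −11.1 with 17%, across repeat runs. The local effect at the cut-off is 0.17 × 55 = 9.4.
- Raw V2-to-V3 change with no effect: A −0.4 to about −7, B +0.6 to about +8. This is regression to the mean, in opposite directions. With 17%, A shows about −12.3 to −18.1 against a true −10.9 to −12.5.

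**The case against.** The strongest reply is that little rests on this model. It is an addition to exploratory secondary analyses. The article says that all analyses are descriptive and that intervals and p-values will be read only descriptively. The primary endpoint is a single-group proportion with an exact interval, and the sample size rests on that alone. The Limitations section already disclaims comparison. All of this stands, and it limits the severity. It does not repair the estimate: a descriptive label deals with error control, not with a number that usually points the wrong way. A planned A-versus-B model also sits badly with a study that calls itself non-comparative.

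A reader might infer more than the article supports:

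- *That the group effect will be tested at 5%.* The two-sided 5% level is attached to the paired t-tests; the ANCOVA sentence states no level.
- *That the LDL-C sign must be wrong.* One of nine scenarios has the right sign and another is close to zero. The spread parameters are assumptions.
- *That every laboratory comparison is biased in the same way.* All figures here are for LDL-C. Total cholesterol follows because it contains LDL-C. For HDL-C, triglycerides, uric acid and creatine kinase, neither size nor direction can be derived.
- *That adjusting for V2 LDL-C is mere extrapolation because the groups do not overlap on it.* Assignment follows a known cut-off, so a contrast near that cut-off can be estimated if the V2 relation is close to linear.

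One could also read the ANCOVA as using change from week 6. The endpoint definition says otherwise. With study-start adjustment only, that version would be biased the other way (about −1 to −18 mg/dL with no drug effect).

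**Conclusion.** The point holds for LDL-C and, by the same mechanism, for total cholesterol. As specified, the group term does not estimate the effect of adding bempedoic acid. With a true 17% reduction (about −11 to −12.5 mg/dL in Group A), the expected A−B difference at week 14 is about −2 to +22 mg/dL, wrong-signed in 8 of 9 scenarios. At week 6 it is about +17 to +38 mg/dL before any bempedoic acid is given. With an inert drug it would be about +8 to +34 mg/dL at week 14.

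The sizes depend on the assumed response SD and visit CV and on the earlier cohort's baseline distribution. The upward direction of the bias was the same in all nine scenarios. This should be fixed before analysis, but it is not a threat to the trial's main result: the Group A responder proportion and its interval do not use this model.

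**What to change.** For LDL-C and total cholesterol, remove the between-group ANCOVA on change from study start, which also brings the section into line with the Limitations.

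In its place, report Group A's V2-to-V3 mean change with a 95% CI. State that Group A was selected for high V2 values, so regression to the mean inflates the apparent reduction. Do not present Group B's V2-to-V3 change as drift on unchanged therapy: it regresses upward, and setting it beside Group A's change would flatter the drug.

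If a between-group estimate is wanted, model V2-to-V3 change on V2 LDL-C and group. Describe the result only as a contrast near the 55 mg/dL cut-off, resting on a near-linear V2 relation.

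The cost is a change of wording and one exploratory comparison lost or replaced. No new data are needed, because the study calendar already has lipids measured at V2 and V3.

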## Pharmacovigilance

Adverse events will be recorded for all participants from the first application of bempedoic acid (or the equivalent time point for the double therapy group) until the last study visit. The safety of add-on treatment with bempedoic acid on top of atorvastatin and ezetimibe background therapy will be assessed by descriptive comparison of (serious) adverse events between the two treatment arms. This safety assessment (as detailed in Table 1) includes but is not restricted to the repetitive measurement of uric acid and creatine kinase as well as the assessment for tendon-related or other muscle-associated potential side effects.

## Trial status

The study design described corresponds to protocol version 3.0 dated 13 November 2023. Patients were recruited between July 2023 and March 2026.

## Limitations

The study has a single-center, open-label, non-randomized design, which introduces potential bias. For example, the single-arm design inherits the risk that changes in food intake, general lifestyle, and background medication over time may influence LDL-C and, thereby, the estimate of LDL-C-lowering effects of bempedoic acid. Hence, our study is exploratory regarding the escalation strategy and non-comparative.

HACOL-ACS is a short-term feasibility trial testing the applicability of sequential add-on bempedoic acid when guideline-recommended LDL-C targets are not achieved with tolerated high-intensity statin treatment combined with ezetimibe. The purpose of the trial is to describe the extent of additive LDL-C lowering provided by the sequential escalation. Given the small sample size and short duration, the trial does not assess long-term outcomes and, therefore, relies on surrogate endpoints, limiting clinical inference.

The single-center design and the fact that the study will be conducted within a specific healthcare system with defined prescribing constraints will impact but not prevent external validity and applicability to other settings. However, these prescribing constraints would have similar applicability even in a multicenter trial in a single country. The constraints on lipid-lowering therapy, however, allowed for prescription of atorvastatin, rosuvastatin, and ezetimibe, which will allow to use the most potent statins.

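### The only planned Group A versus Group B model omits week-6 LDL-C, the value that assigns treatment; a V3-on-V2 model using data already collected would describe the add-on effect better

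*Protocol article*

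**What the plan says.** The Limitations section of the protocol article states the aim: "The purpose of the trial is to describe the extent of additive LDL-C lowering provided by the sequential escalation". It warns that "the single-arm design inherits the risk that changes in food intake, general lifestyle, and background medication over time may influence LDL-C", and concludes: "Hence, our study is exploratory regarding the escalation strategy and non-comparative". The Background section is more ambitious and promises to show exactly what bempedoic acid adds in each patient.

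Treatment in Stage II follows a fixed rule on LDL-C at V2 (Study intervention/treatment). Bempedoic acid "will be given at V2 to patients with LDL-C 1.4-2.8 mmol/L (55-110 mg/dL) (Group A"; "patients with LDL-C < 1.4 mmol/L (55 mg/dL) will be continued on the background medication with the previous dosing (Group B". Above that range, "Patients with LDL-C > 2.8 mmol/L (110 mg/dL) at week 6 will be directly referred for PCSK9 inhibition outside the trial". Everyone at or below 2.8 mmol/L "will have a revisit (V3) after another 8 weeks, including another lipid test".

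Statistical analysis plans paired t-tests within each group for continuous data. It also plans a comparison of mean changes in laboratory parameters between Groups A and B, "using an analysis of covariance model, including baseline values at the start of the study and group assignment".

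**The concern.** Group membership is a deterministic function of V2 LDL-C. A comparison of later LDL-C between the groups that does not condition on V2 compares patients chosen for high values with patients chosen for low values. The study-start value does not repair this, because two patients with the same admission LDL-C can fall on opposite sides of the cut-off at week 6. The planned group coefficient for LDL-C therefore carries the selection as well as the drug.

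The other route, the paired change within Group A, has no reference group. Group A is selected on a high measurement, so part of its fall to V3 is regression to the mean. Any 8-week drift is added to that.

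Neither analysis serves the stated purpose well, although the design contains what a better one needs: a sharp assignment rule on a recorded variable, about half the patients on each side, and the same lipid test 8 weeks later in both groups. This is a regression-discontinuity structure.

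**Working it through.** **Inputs from the article.** Add-on effect 17% (Background). About half of patients miss the target at week 6, maximum 135 patients, 5% drop-out (Sample size). Study-start LDL-C 3.9 ± 0.7 mmol/L (Study population and inclusion). 135 × 0.95 gives about 128 patients.

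**Assumed, not in the article.** Between-person SD of log LDL-C on dual therapy, τ = 0.30 to 0.45. Within-person SD per measurement, ω = 0.10 to 0.20. Drift of -10%, -5% or +5%.

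**1. The plan's own figure.** With 30 responders of 60, the Clopper–Pearson interval is 0.368 to 0.632, width 26.4%, as stated. This sizes a proportion; the plan gives no precision for the additive effect.

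**2. Selection in the A-versus-B comparison.** Let s = √(τ² + ω²) be the SD of log V2, and ρ = τ²/s² the slope of log V3 on log V2. With a cut at the median, the expected A minus B gap at V3 with no drug effect is ρ × 2s × √(2/π) = 1.596 ρs. The drug contributes ln 0.83 = -0.186.
- τ = 0.30, ω = 0.10: s = 0.316, ρ = 0.90, gap 0.454; net +0.268.
- τ = 0.30, ω = 0.20: s = 0.361, ρ = 0.692, gap 0.398; net +0.212.

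Both are positive, although the true effect is negative (about 0.17 × 1.4 = 0.24 mmol/L lower). This hand check ignores the study-start covariate and the exclusion above 2.8 mmol/L. Simulation of the ANCOVA on study-start baseline and group (2,000 trials per scenario, change taken from study start to week 14) gave +0.26 to +0.54 mmol/L without drift. A separate simulation gave about +0.15 to +0.43. With no drug effect the coefficient was about +0.73 (τ = 0.35, ω = 0.10). The more closely V2 LDL-C follows the study-start value, and the smaller τ is, the nearer the coefficient moves to zero. The sign can therefore be wrong, but it need not be in every case.

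**3. Change within Group A.** Regression to the mean adds -(1 - ρ) × s × √(2/π) on the log scale.
- τ = 0.30, ω = 0.10: 0.10 × 0.316 × 0.798 = 0.025; 0.83 × e^(-0.025) = 0.81, a change of -19%.
- τ = 0.30, ω = 0.20: 0.308 × 0.361 × 0.798 = 0.089; 0.83 × e^(-0.089) = 0.76, a change of -24%.

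Simulation, which includes the upper exclusion, gave -18.0% to -22.4% without drift. With common drift of -5% or +5% it gave -22.5% or -14.3% (ω = 0.10), and with -10% it gave -27.9% (ω = 0.15).

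**4. Model conditioning on V2.** log V3 = α + β(log V2 - log cut-off) + δ × [Group A]. Common drift goes into α; selection and regression to the mean go into β. Simulated e^δ - 1 was -16.8% to -17.1% without drift and with common drift of -10%, -5% or +5%.

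**5. Precision.** Because group and V2 are correlated, the variance exceeds that of a randomised comparison by 1/(1 - 2/π) = 2.75. With residual SD σ, SE = σ × √(4 × 2.75/128) = 0.293σ, where σ² = ω² + τ²ω²/s².
- τ = 0.30, ω = 0.10: σ = 0.138, SE 0.040 (simulated 0.042).
- τ = 0.30, ω = 0.20: σ = 0.260, SE 0.076 (simulated 0.081).

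Across scenarios the simulated SE was about 0.04 to 0.09. The 95% CI around -17% is e^(-0.186 ± 1.96 SE) - 1: about -24% to -10% at SE 0.042, and -30% to -1% at SE 0.090. The chance that the interval excludes zero was about 0.99, 0.76 to 0.83 and 0.53 to 0.62 at ω = 0.10, 0.15 and 0.20. Restricted to V2 of 1.0 to 1.8 mmol/L (about 55 to 75 patients), it ran from 0.84 down to 0.23.

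**6. Drift in Group B only.** The model then estimates 0.83/(1 + d).
- d = +5%: 0.790, or -21%.
- d = +10%: 0.755, or -25%.
- d = -5%: 0.874, or -13%.

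Simulation gave -21.0%, -24.6% and -12.8%.

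**The case against.** The strongest reply is that the article makes no false claim here. It discloses the limits of an open-label, non-randomised study, labels its comparisons exploratory, and has a primary endpoint (a responder proportion with an exact interval) that is untouched. Extra models may be in a statistical analysis plan that is not shown. This stands as far as it goes: the primary analysis is not at fault, and the absence of a regression-discontinuity model would not by itself be a finding. But the article does fix a between-group model and names its covariates, and for LDL-C that choice is poor for the purpose the article states.

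A reader might infer that the V2-adjusted model gives a drift-free effect. The documents do not support that. The trial is open-label, group assignment tells patients and physicians who missed the target, and physicians' statin escalation or switching counts as stable baseline medication. Diet, adherence or statin use can therefore change differently on the two sides of the cut-off, and step 6 shows that this passes straight into the estimate. Nor does the article concede that the drug effect cannot be separated from drift; it says only that drift may influence the estimate. And Group B is not unused: an A-versus-B comparison is planned, with the wrong baseline for this purpose.

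Two further limits stand. The effect is that at about 1.4 mmol/L, whereas Group A extends to 2.8 mmol/L and the trial asks how many of that group reach target. The good simulated performance also comes from data generated with the linear form that was fitted.

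**Conclusion.** The point holds as a cheap improvement to an exploratory analysis; it does not invalidate the trial. For LDL-C, the planned ANCOVA coefficient mainly reflects who was selected into Group A and can have the wrong sign: +0.26 to +0.54 mmol/L in one set of simulations and +0.15 to +0.43 in another, against a true effect of about -0.24 mmol/L. The within-Group-A change can be several percentage points off, by more when there is drift. Conditioning on V2 removes regression to the mean and drift common to both groups, and recovered about -17% in those scenarios.

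The direction of the argument follows from the assignment rule. The sizes rest on the assumed between-person and within-person SDs, on a split near the median, on approximate linearity in log LDL-C, and on reading the ANCOVA as change from study start to week 14, as the secondary endpoints define it. The estimate would be local and only moderately precise, and would remain exposed to differential drift. It supports a better-founded description of the add-on effect, not a claim equivalent to randomisation.

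**What to change.** For LDL-C, replace or supplement the planned ANCOVA with an exploratory model, for example:

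*Linear regression of log LDL-C at V3 on log LDL-C at V2, centred at the cut-off in the unit actually used for assignment, and a Group A indicator, in all patients with V2 LDL-C ≤ 2.8 mmol/L. The group coefficient is reported as the percent difference at the cut-off with a 95% CI.*

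- Sensitivity analyses: separate slopes by group; a narrower window around the cut-off; exclusion of patients whose statin changed after V2.
- Tabulate background-medication changes after V2 by group, so that readers can judge differential drift.
- State which unit defines the cut-off, since 1.4 mmol/L is about 54 rather than 55 mg/dL.
- Keep the caveat in Limitations. Add that this estimate removes regression to the mean and drift common to both groups, but not drift that differs between groups at the cut-off, and that it applies only near 1.4 mmol/L. Bring the Background claim about the exact additive impact into line.

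The cost is a few lines of plan and one regression with its sensitivity analyses. No new data are needed, and the primary endpoint and sample size do not change. The downsides are a local estimate, dependence on linearity, and a log-scale SE of about 0.04 to 0.09 under the assumed within-person SDs.
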